### Adjudication of outcomes

Adjudication of all outcomes will be performed by investigators who will be blinded to the treatment allocation. The Image analysis of the CT-derived AVC volume scores for the study will be performed centrally by two independent imaging specialists, also blinded to the treatment allocation. AVC volume scores^43^ will be calculated using vendor independent software (OsiriX, Version 5.8.5).

### Safety measures

The risks associated with participation in this research project are expected to be minimal.^37^ However, all adverse events will be systematically documented and reported in accordance with the Good Clinical Practice guidelines.

Participants will be reviewed at 3-month intervals throughout the study period to monitor clinical status and assess for any emerging concerns. The trial team will be specifically vigilant for increased risk for developing venous thromboembolism and blood dyscrasias. Participants will receive a dedicated contact phone number and email address to reach the study coordinators directly for support of queries. They will be requested to notify the trial team promptly in the event of hospital admission or any significant health event. The primary care physician for each participant will be informed of their enrollment in the trial and provided with contact details for the trial coordination team.

These measures are intended to ensure timely identification and appropriate management of any safety issue, which might arise during the trial.

## Study status

The protocol for the PASSPORT trial was approved by the human research ethics committees of Royal Perth Hospital and the East Metropolitan Health Service (Project Reference Number: RGS 0000005161) and is registered with the Australian New Zealand Clinical Trials Registry (ACTRN12622000447752). Recruitment for the PASSPORT trial began in July 2023 and was completed on 01 July 2024. By that date, 108 participants were randomized into the trial. The baseline characteristics of the participants randomized to PASSPORT are described in *Table 3*.

**Table 3 oeaf144-T3:** Baseline characteristics of participants randomized into the PASSPORT trial

Characteristic	Randomized patients (*n* = 108)
Demographics	
Age (years), mean (SD)	73 (± 8.9)
Male, *n* (%)	73 (67.6%)
CAS severity (as per pVel on TTE)	
Mild, *n* (%)	74 (68.5%)
Moderate, *n* (%)	34 (31.5%)
Initial CTAVC score (Agatston units^a^), Median (IQR)	716 (413–1424)
Hypertension, *n* (%)	71 (65.7%)
Diabetes mellitus, *n* (%)	26 (24.0%)
Hypercholesterolemia	64 (59.3%)
BMI (kg/m2), mean (SD)	28.7 (± 4.8)
Current smoker, *n* (%)	4 (3.7%)
Medication use at baseline	
ACEi/ARB, *n* (%)	67 (62.0%)
Statin, *n* (%)	66 (61.1%)
Beta-blocker, *n* (%)	30 (27.8%)
NDP CCB, *n* (%)	5 (4.6%)

^a^Though Agatston units is provided in this table of baseline characteristics, the primary outcome of the PASSPORT trial is change in calcium volume. Change in Agatston units is a secondary outcome.

*ACEi*, Angiotensin-converting-enzyme inhibitor; *ARB*, angiotensin receptor blocker; *BMI*, body mass index; *CAS*, calcific aortic valve stenosis; *CKD*, chronic kidney disease; *CTAVC*, computed tomography aortic valve calcification; *NDP-CCB*, non-dihydropyridine calcium channer blocker; *pVel*, peak blood flow velocity through aortic valve; *SD*, standard deviation; *TTE*, transthoracic echocardiography.

As of 6 March 2025, four participants have dropped out of the trial, three required aortic valve replacement surgery, and one was diagnosed with stage 4 cancer. A total of 104 participants continue on the trial. No adverse effects related to the investigational product have been identified.

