## Methods and analysis

### Study design, inclusion and exclusion criteria

PASSPORT will be a prospective, investigator-initiated, single-centre, double-blind, randomized, controlled trial, conducted in Royal Perth Hospital, Australia. A total of 108 adult participants with mild or moderate aortic stenosis will be randomized 1:1 to either vitamin K1 or a matched placebo for an average of 16 months (*Figure 1*).

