### Adherence and withdrawal from trial

To assess adherence to the investigational product, participants will complete the Brooks Medication Adherence Scale, and pill counts will be performed at each follow-up visit. The Brooks Medication Adherence Scale will be used due to its concise, 4-question, yes/no format which will provide information on both unintentional and intentional non-adherence to the investigational product. Additionally, the change in ucOC/tOC from the baseline and final visits will be compared which will provide information on adherence to the vitamin K1 for participants in the treatment arm.

Participants may leave the study by withdrawing their consent to participate at any time and for any reason. Any data collected until the date of withdrawal will be retained and used in the final analysis.

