### Statistical considerations

The primary intention-to-treat analysis will evaluate the within-group change in CT-derived AVC volume scores between baseline and study end (mean 16 months, minimum 12 months, maximum 21 months), using a repeated-measures general linear model. The model will include fixed effects for treatment group (vitamin K1 10 mg/day vs. placebo), duration of follow-up (baseline to final visit), and their interaction (treatment × duration of follow-up), with subject as a random effect. Baseline covariates (e.g. age, sex, baseline AVC score) will be included to adjust for potential confounders. The *treatment × time* interaction will estimate and test the between-group difference in mean AVC change, assessing whether the active treatment significantly attenuates AVC progression compared to placebo. Model assumptions (normality, homogeneity of variances) will be verified using diagnostic plots and tests, with transformations applied if needed.

A prior open-label study, using CT-derived AVC volume quantification, reported a 103μL (57%) lower AVC progression in 38 subjects who received vitamin K1 (2 mg per day) for 12 months when compared with 34 control subjects.^31^ Based on this, the PASSPORT trial, which will have 54 subjects per study arm (total 108), will provide 90% power to detect a 57% difference in AVC progression (181 μL in controls vs. 78 μL for active treatment) between the groups, assuming a common standard deviation of 165 μL. This sample size will also provide 80% power to detect a 49% difference and 70% power to detect a 40% difference, at a significance level of 5%. We anticipate a low dropout rate of 5–10% based on previous experience with similar cardiovascular trials,^37^ supported by robust follow-up procedures and regular participant contact. However, in the event of a loss to follow up of up to 25% (from 54 to 41 subjects per arm), the trial would retain 80% power to detect the primary effect (57% difference in AVC progression).

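### Valve replacement is recorded as dropout and no CT is scheduled before it, so the primary outcome can be lost through an event plausibly related to progression

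*Protocol article*

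**What the plan says.** The Study status section states that "four participants have dropped out of the trial, three required aortic valve replacement surgery, and one was diagnosed with stage 4 cancer", and that 104 participants continue. Since 104 + 4 = 108, the three valve replacements are counted as having left the trial.

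Table 2 (Trial duration/schedule) lists the CT calcium scan at baseline and the final visit only, and Follow-up and trial termination ties the repeat investigations to that final visit. Under Study outcomes, the primary outcome is follow-up minus baseline calcium volume, divided by the time between the two scans.

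For those who leave, Adherence and withdrawal from trial says: "Any data collected until the date of withdrawal will be retained and used in the final analysis". Statistical considerations calls the main comparison "The primary intention-to-treat analysis", fitted as a repeated-measures model with a treatment-by-time term and baseline covariates. That section discusses loss to follow-up only in terms of power: 5–10% expected, and 80% power retained after a 25% loss.

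**The concern.** The outcome needs two scans. Someone who leaves before the final visit has only the baseline one, so retaining data up to withdrawal keeps no change to analyse. Such a participant can stay in the mixed model but adds essentially nothing to the treatment-by-time term. The estimate then depends on the missing changes being predictable from baseline.

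That is doubtful for valve replacement. The abstract describes replacement as the treatment for severe, symptomatic disease, while the trial enrols only mild or moderate stenosis. The background names calcium build-up as the main driver of the disease. Someone who needs a new valve during follow-up has therefore plausibly progressed, and the native valve cannot be scored afterwards.

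The power allowance for dropout does not cover this, because the risk is bias rather than lost numbers. If more replacements fall on placebo, its mean progression is understated and the effect shrinks. If more fall on vitamin K1, the effect is inflated.

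**Working it through.** **Inputs (Statistical considerations and Study status).** Mean progression "181 μL in controls vs. 78 μL for active treatment", so the difference is 181 − 78 = 103 μL; "assuming a common standard deviation of 165 μL"; 54 per arm; alpha 5%, taken as two-sided because that reproduces the stated power. Losses: 4 of 108 (3.7%), of which replacements 3 of 108 (2.8%).

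**1. The plan's own power.** Standard error = 165 × √(2/54) = 31.8 μL. 103/31.8 = 3.24, and Φ(3.24 − 1.96) = 90.0% (noncentral t: 89.5%). With 41 per arm, 103/(165 × √(2/41)) = 2.83, and Φ(2.83 − 1.96) = 80.7% (noncentral t: 79.7%). Both stated figures reproduce.

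**2. If the three losses were unrelated to progression.** With 54 and 51 analysed and the difference still 103 μL, power is 88.6% (noncentral t). Lost numbers alone hardly matter.

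**3. Shift of an arm mean.** If k participants in an arm of 54 lie on average m SD above the full-arm mean and are missing, the mean of the other 54 − k is low by k × m × 165/(54 − k). For k = 3:

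- m = 1: 3 × 1 × 165/51 = 9.7 μL
- m = 2: 3 × 2 × 165/51 = 19.4 μL

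Under a Normal distribution the top three of 54 lie about 1.94 SD above the mean on average, which gives 3 × 1.94 × 165/51 = 18.8 μL. Average distances much beyond 2 SD are therefore implausible under this model.

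**4. Effect by split between arms.** Simulation of 54 per arm, Normal(181, 165) against Normal(78, 165). The largest progressors of the relevant arm are deleted, then a two-sample t-test is applied. That the three are the largest progressors is an assumption.

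| Replacements placebo:active | Expected difference (μL) | Power |
|---|---|---|
| none | 103 | about 90% |
| 3:0 | 84 | about 77% |
| 2:1 | 97 | about 87% |
| 1:2 | 109 | about 94% |
| 0:3 | 122 | about 97% |

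The higher power in the last two rows comes from an inflated difference and is no gain.

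**5. No true effect.** Deleting the top three from one arm moves the difference by about 19 μL and raises the two-sided rejection rate from about 5% to about 10% in that split. A 2:1 split moves it by about 6 μL. If loss depends on progression equally in both arms, no bias is expected under the null.

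**The case against.** The strongest reply is that much of this is inference. The article does not say that the three had no second scan. Participants are seen every three months and asked to report hospital admissions, so the team could have learned of planned surgery and scanned beforehand. This stands: the absence of a scan follows from the schedule and is not reported.

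A reader might also infer that the fastest progressors are known to have been removed. The documents do not support that. No progression data are given for the three, and symptoms can prompt surgery. The Discussion notes that about a quarter of people with severe stenosis have lower calcification because fibrosis dominates. Replacement may also reflect greater severity at entry, since 34 of 108 had moderate disease. Baseline calcium is a model covariate and severity a stratification factor, which makes ignorable loss less implausible but does not establish it.

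A reader might further infer that losing the participant with cancer departs from intention to treat. That cannot be concluded, because withdrawal of consent would explain it equally well.

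Finally, handling of missing data usually belongs in the statistical analysis plan, which is not shown, so its absence from the article is no error. The reply does not reach the data-collection point: no analysis plan can recover a scan that was never taken. It is also true that an earlier scan cannot help the three already lost. It can serve only those still in follow-up.

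**Conclusion.** The point holds as a cheap improvement and is not a demonstrated bias. As written, the schedule lets an outcome-related event remove the primary measurement, and that event accounts for three of the four losses reported so far. The article treats such loss only as lost power under an intention-to-treat label.

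The size is modest at 2.8% of participants, and the direction is unknown because the arms are not given. Under the assumption that the three are the largest progressors of their arm, the expected difference runs from about 84 to about 122 μL around the planned 103 μL, and a mixed split moves it by only about 6 μL. These figures also assume Normal progression with SD 165 μL and no second scan for any of the three. The count could still rise, since follow-up was continuing at the date of the report.

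**What to change.** For participants still in follow-up:

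- Obtain the already planned final CT and echocardiogram before valve replacement, with consent and without delaying care. Annualize by the actual interval and include these scans in the primary analysis.
- Distinguish stopping capsules from withdrawing consent, and keep those who only stop capsules in follow-up for the final scan.

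For replacements without a pre-operative scan, including the three already lost if none exists:

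- Pre-specify, before unblinding, one sensitivity analysis that does not assume missing at random. This can be a worst-rank comparison with replacement ranked worst, or a delta/tipping-point analysis with the shift varied separately by arm.
- Report the number of replacements by arm.

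The cost is small: a planned scan is moved earlier and one analysis is added. The drawback is that annualized values over shorter intervals are noisier.

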## Discussion

The PASSPORT Trial will provide information on the efficacy of oral vitamin K1 supplementation for the secondary prevention of CAS. A previous open-label randomized controlled trial which showed that vitamin K1 reduced AVC progression analysed data from 72 patients and included participants with aortic sclerosis.^31^ The PASSPORT trial aims to build on this knowledge by using a double-blind approach, recruiting a larger participant cohort (*n* = 108), increasing the duration of follow-up (mean participant duration of 16 months), and including only patients who have mild or moderate CAS.

A potential limitation of this trial is confounding by dietary vitamin K1 intake and baseline vitamin K1 status, which may vary between participants and might obscure the effect of vitamin K1 supplementation. To address this, baseline and final blood tests will measure the ucOC/tOC, a validated biomarker of vitamin K1 status. Each participant will also have a baseline dietary nutritional intake assessment, using the DQES V3.2 questionnaire,^38^ which has been developed and validated for assessing food and nutrient intakes in Australia.^45,46^ Although the DQES V3.2 does not directly quantify vitamin K1 intake, estimated intake will be derived from key foods using published nutrient databases. Baseline ucOC/tOC and estimated dietary vitamin K1 intake will be included as covariates in the repeated measures general linear model alongside other baseline covariates to adjust for potential confounding. Exploratory sensitivity analyses will assess treatment effect heterogeneity by baseline vitamin K1 status to evaluate if dietary or baseline status attenuates the effect of supplementation. Another potential limitation of the trial is the use of non-contrast CT. CT AVC quantification correlates well with CAS disease severity in most patients,^47^ but this modality does have some limitations. Approximately a quarter of individuals with severe CAS, particularly among females, younger patients, and those with a bicuspid valve, have lower levels of valvular calcification because in these cohorts the disease is predominantly driven by fibrotic change.^7,48^ However, CT demonstrates excellent scan-rescan reproducibility when measuring AVC volume, density, and Agatston units and is therefore a dependable modality to measure AVC progression, which is the primary outcome of this trial. Whilst women likely will have less calcification at baseline and progress at a slower rate than men, the randomization is likely to ensure equal distribution of sex across treatment groups.^49^

It is well established that vitamin K is crucial for the maintenance of effective coagulation and the minimum daily intakes recommended by the National Institute of Medicine (90–120 µg/day) and the European Food safety Authority (70 µg/day)^35,36^ were formulated based on the presumption that haemostasis is the only metabolic process in which vitamin K is involved. The importance of this cofactor in maintaining the integrity of the vasculature has only been recognized relatively recently, and the exact daily dosage needed to optimize this remains unknown.^50,51^ Multiple studies have suggested that vitamin K1 supplementation reduces calcification not only in the aortic valve but also in the peripheral and coronary arteries.^25,26,32,52^ It is possible that the currently recommended daily intake may need to be revised to a higher dose.

PASSPORT is the only trial currently registered to test the hypothesis that vitamin K1 prevents calcification of the aortic valve.^32^ If vitamin K1 supplementation proves effective, it would be the first proven pharmacotherapy for the treatment of CAS and would dramatically alter the global therapeutic landscape for this deadly condition, where a high-risk, high-cost valve replacement is currently the only known definitive treatment. It is likely that oral supplementation with vitamin K1 would be incorporated into clinical practice and guidelines as a low-cost, safe, and effective treatment for non-severe CAS. It stands to reason that subgroups of patients who manifest a predominantly calcific phenotype of CAS, older and male patients,^7^ might benefit most from the anti-calcific properties of vitamin K1. The randomization was also stratified by severity of CAS, which would enable an exploratory analysis assessing if vitamin K1 is more effective in mild rather than moderate CAS. More broadly, if the PASSPORT trial has a positive result, it would enhance our understanding of the physiological role that vitamin K1 plays in optimizing vascular health and provide a rationale for further studies to examine any role in reducing the progression of calcification in other locations. If the trial is negative, it will provide an important answer in our quest to find a medical treatment for CAS and will guide researchers towards investigating other potential therapeutic targets for this disease.

## Data Availability

The baseline characteristics table presented in this manuscript summarizes data from recruited participants in the PASSPORT trial. Individual participant data and additional datasets generated for the PASSPORT trial will be made available upon reasonable request to the corresponding author following completion of the study, subject to ethical approval and applicable data protection regulations. All data requests should specify the purpose of the data request and will be reviewed by the trial steering committee.
